## Methods/design

### Overview

ACCESS-ESLD (A Rapid, Non-invasive, Clinical Surveillance for CachExia, Sarcopenia, Portal HypertenSion, and Hepatocellular Carcinoma in End-Stage Liver Disease) is a multi-center prospective cohort study aiming to include 150 patients with liver cirrhosis. Patients with established liver cirrhosis will be included and repeated abbreviated MR-examinations will be performed instead of ultrasonography at baseline, 6 months, 12 months, and 18 months, i.e., with a 6-month interval. This interval is currently recommended and used in normal clinical care for surveillance of HCC in these patients. The MR-examination will include body composition profiling (BCP; for e.g.*,* sarcopenia [via MAsS] and portal hypertension [via spleen volume]) and HCC-screening. Patients will be consecutively enrolled at the department of Gastroenterology and Hepatology, University Hospital in Linköping, County Hospital in Jönköping (Ryhov) and District Hospital in Eksjö (Höglandssjukhuset). A detailed medical history as well as a comprehensive list of clinical data, biochemical investigation, tests of physical function and mobility, and biological samples will be obtained in all individuals.

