### Estimation of sample size and power calculation

One of the main objectives of the study concerns sarcopenia in patients with cirrhosis, and sarcopenia is therefore the basis for our power calculations. Previous imaging-based studies on muscle mass and composition in patients with cirrhosis have found sarcopenia to be prevalent in a range of 30 to 70% of patients [19].

At the time of the study design, there were limited numbers of studies with longitudinal follow-up of muscle loss in a somewhat comparable way. One of these studies has shown that an annual loss of muscle volume of − 3.1% (measured by computer tomography) is significantly associated with a high risk of mortality in this patient group [20]. We have previously shown that we can measure muscle volume with a precision of 0.8–1.5% (coefficient of variation) [21, 22].

To detect a change of − 3.1% in a year with a precision of 1.5% (assuming upper limit for safety) and a risk of incorrectly rejecting our hypothesis (α) of 5% and a statistical power (1-β) of 90%, would require a population size of 47. We should reach this population size, with margin, with a total population of 150 people, if about 60% will suffer from muscle loss and we take heed for loss due to e.g.*,* technical errors, study persons who choose to refrain from continued participation, and other unpredictable events that may affect data collection and its quality. A frequently used statistical power of 80% requires 35 people, and we can then assume that if our population is in the low 30% that will suffer from muscle loss, we can still expect to see differences/effects.

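### The sample sizes of 47 and 35 do not follow from the stated 3.1% change and 1.5% precision, and the SD of annual change is never given

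*Protocol article*

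**What the plan says.** The protocol article, under *Estimation of sample size and power calculation*, bases the power calculation on muscle loss. The target is an annual change of −3.1%, taken from a CT study that linked that rate of loss to mortality. The only variability figure is scan precision: "we can measure muscle volume with a precision of 0.8–1.5% (coefficient of variation". The calculation uses the upper end: "3.1% in a year with a precision of 1.5% (assuming upper limit for safety". The error rate is "a risk of incorrectly rejecting our hypothesis (α) of 5"%, and with 90% power this "would require a population size of 47".

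The section then argues that 47 is comfortably reached "with a total population of 150 people, if about 60% will suffer from muscle loss", after allowing for losses. For the case where only 30% lose muscle it falls back on a second figure: "A frequently used statistical power of 80% requires 35 people".

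No test, sidedness, formula or other SD is given. The design is a single cohort: it "is a multi-center prospective cohort study aiming to include 150 patients with liver cirrhosis" (*Overview*).

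**The concern.** Inputs and outputs are printed side by side, so they can be checked without an analysis plan. A change of 3.1 against an SD of 1.5 is more than two SDs, and an effect that large needs only a handful of patients. A requirement of 47 implies an effect of roughly half an SD.

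The choice of SD is a second problem. Scan precision describes how well one patient's volume is measured. The SD in a test of mean change must also reflect how much true change differs between patients.

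This is the article's only power statement. Both of its adequacy claims, for 60% and for 30% losing muscle, are comparisons with 47 and 35.

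**Working it through.** **Inputs (all from the sample size section).** Change Δ = 3.1%; precision 1.5%; α = 0.05, taken as two-sided because sidedness is not stated; power 90% and 80%; 150 enrolled, so 0.60 × 150 = 90 or 0.30 × 150 = 45 patients losing muscle.

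**Method.** One-sample (paired) t-test of a mean change. The normal approximation is n = (z_α + z_β)² × (SD/Δ)², with (z_α + z_β)² = 10.507 at 90% power and 7.849 at 80%. Exact values use the noncentral t distribution.

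**Step 1: try to reproduce 47 and 35 from the stated inputs.**

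| SD used | Δ/SD | n at 90% (exact) | n at 80% (exact) |
|---|---|---|---|
| 1.5 | 2.07 | 4.75, so 5 | 4.10, so 5 |
| 1.5 × √2 = 2.12 (difference of two scans) | 1.46 | 7.11, so 8 | 5.87, so 6 |

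The normal approximation gives less: 10.507 × (1.5/3.1)² = 2.5 and 7.849 × (1.5/3.1)² = 1.8. One-sided tests need fewer still. A two-group comparison with SD 2.12 needs 11 and 9 per group, or 22 and 18 in total. None of these is near 47 or 35. At n = 47 with SD 2.12, power is above 99.9%.

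**Step 2: swap the two numbers.** With d = 1.5/3.1 = 0.484, the exact t calculation gives 46.84 and 35.49. The normal approximation gives 44.9 and 33.5; adding the usual z_α²/2 = 1.92 gives 46.8 and 35.4. Rounded to the nearest integer, these corrected values are 47 and 35. Power is 90.1% at n = 47 and 79.4% at n = 35.

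**Step 3: work backwards without swapping.** In a two-sided t-test, n = 47 at 90% power implies d = 0.483, so SD = 3.1/0.483 = 6.42%. Likewise n = 35 at 80% implies d = 0.4875, so SD = 6.36%. Taking out two-scan error leaves a between-patient SD of √(6.42² − 2 × 1.5²) ≈ 6%. The article states no such figure.

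**Step 4: what the answer depends on.** Let SD of change = √(2 × 1.5² + s²), where s is the between-patient SD of true annual change. The article gives no value for s, so the values below are assumptions.

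| Assumed s | SD of change | n at 90% | n at 80% |
|---|---|---|---|
| 3% | 3.67% | 17 | 14 |
| 5% | 5.43% | 35 | 27 |
| 8% | 8.28% | 77 | 58 |
| 10% | 10.22% | 117 | 88 |

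Power to detect 3.1% with the article's own expected numbers, before attrition:

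| Assumed s | 90 patients (60%) | 45 patients (30%) |
|---|---|---|
| 6% | above 99% | 89% |
| 8% | 94% | 69% |
| 10% | 81% | 51% |

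**The case against.** Four objections deserve weight.

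**The cause is not shown.** A reader might infer that the authors certainly inverted the effect size. The article does not establish that, because it prints no formula. The match at 80% is also imperfect: 35.49 would conventionally be rounded up to 36. Other routes exist: an SD near 6.4% gives both figures, and so does 2 × (z_α + z_β)² × 1.5²/1², which is 47.3 and 35.3. Each needs an input that the article does not state. Inversion needs only the two printed numbers, so it is the simplest explanation, but it remains an inference. One detail counts against a deliberate swap: the upper precision limit is chosen for safety, yet with the ratio inverted a larger precision value lowers n. Using 0.8/3.1 instead would give 160 and 120.

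**The error is in the cautious direction.** On the stated inputs, 47 overstates the need. That stands, and a reader should not infer that 150 patients are too few; nothing in the document shows it. With 90 patients, power is still 81% at an assumed s of 10%. Any caution is accidental, however.

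**The 5 to 8 are not valid sample sizes either.** Agreed. The √2 step assumes that the precision refers to a single scan, and both values ignore between-patient variation. They show only that the printed numbers do not fit.

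**The range for s is not from the document.** Agreed. It is an assumption and cannot show which n is right. In particular, it does not show that the 30% scenario fails: 45 patients suffice for 80% power at s = 6% but not at 8%.

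**Conclusion.** The concern holds in this form: 47 and 35 do not follow from a 3.1% change, 1.5% precision and 5% alpha under any standard variant tried. On those inputs a two-sided one-sample or paired test gives about 5 to 8 patients at 90% power and 5 to 6 at 80%. An inverted ratio is the likely cause but is not proven.

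The more consequential gap is that the SD of annual change between patients is missing. Without it, reaching the required size comfortably at 60%, and still seeing effects at 30%, are assertions that the printed calculation does not support. The 30% claim is the weaker one: power with 45 patients runs from 89% to 51% as the assumed between-patient SD goes from 6% to 10%.

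This rests on reading the calculation as a test of mean within-patient change, the natural reading for a single cohort. Severity is should-fix: the only power statement is wrong as written, but the error does not show enrolment to be inadequate.

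**What to change.** Rewrite the sample size paragraph:

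- Withdraw 47 and 35.
- Name the test and its sidedness.
- Give a justified SD of annual change that combines scan error with between-patient variation, for example √(2 × 1.5² + s²) if the 1.5% is a single-scan figure. Say where s comes from.
- If no source for s exists, give the required n over a range labelled as an assumption, such as 17, 35, 77 and 117 at 90% power for s = 3%, 5%, 8% and 10%.
- Keep 150 enrolled. Restate the power, or the smallest detectable change, for the expected 90 and 45 patients losing muscle, with attrition allowed for.

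The cost is one rewritten paragraph, with no change to enrolment, visits or procedures.

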### Study procedure

Following the provision of informed consent, patients will be assigned a unique study-participate identification code incorporating the recruitment site identifier. All data will be link-anonymized throughout the study, recorded through a secure web-based application for electronic data (REDCap™, https://projectredcap.org/software/).

A member of the research team will complete a clinical report form on clinical data (Table 2). Questionnaires regarding lifestyle and self-reported quality of life will be obtained, fitness and physical activity will be assessed, and baseline clinical biochemistry will be obtained.

**Table 2 Tab2:** Layout of the anthropometric and clinical data collected at inclusion and at each visit^a^

Categories of Data	
**Basic data**	
• Date of birth	
• Gender	
• Anthropometrics	
◦ Height	
◦ Weight	
◦ Waist circumference	
◦ Hip circumference	
◦ Blood pressure	
**Previous and present cirrhosis history and severity**	
• Date and modality of cirrhosis diagnosis	
• Underlying etiology	
• Decompensating event (type and date)	
**Assessment of hepatic encephalopathy**	
• Animal naming test	
**Medical History**	
• Previous and present relevant comorbidities and date of diagnosis, including:	
◦ Hypertension, dyslipidemia	
◦ Cardiovascular diseases, including PCI and CABG	
◦ Congestive heart failure	
◦ Atrial fibrillation/flutter	
◦ Stroke	
◦ Malignancies	
• Current or recent medication (including over-the-counter, traditional/herbal remedies, and nutritional supplements)	
**Family History**	
• Family medical history	
**Lifestyle**	
• Smoking – Yes/No/Ex, and frequency of smoking (pack-years)	
• Coffee consumption – cups/days	
• Alcohol consumption	
• Physical activity and fitness	
• Patient reported quality of life	
• Sleep quality assessment	
**Hand grip strength**	
**FibroScan**	
• VCTE	
• CAP	
**MR-examination (20 min)**	
• Body composition: VAT, ASAT, liver PDFF, thigh FFMV and MFI, spinal erector FFMV and MFI, liver volume, and spleen volume.	
• Muscle Assessment Score (MAsS): MVZ and sex-adjusted MFI	
• L3-SMI	
• Liver MRE	
• HCC screening	
**Muscle function and physical frailty**	
• Short physical performance battery (SPPB)	
• Hand grip strength (HGS)	
• Liver frailty index (LFI)	

^a^Follow-up occurs every 6 months, in total 4 MR-examinations. If a lesion defined as LI-RADS-3 is discovered, the interval for surveillance with MRI is shortened to every 4 months for 12 months, in total 5 MR-examinations. If HCC is discovered, study participants’ continuation in the study is seized

*Abbreviations:*
*CABG* coronary artery bypass graft, *CAP* controlled attenuation parameter, *FFMV* fat-free muscle volume, *L3-SMI* skeletal muscle index at the 3rd lumbar vertebrae, *MFI* muscle fat infiltration, *MRE* magnetic resonance elastography, *MVZ* muscle volume z-score, *PCI* percutaneous coronary intervention, *PDFF* proton density fat fraction, *ASAT* abdominal subcutaneous adipose tissue, *VAT* visceral adipose tissue, *VCTE* vibration controlled transient elastography

Included patients are invited for a study visit at the Department of Gastroenterology and Hepatology, University Hospital in Linköping, County Hospital in Jönköping or District Hospital in Eksjö (Fig. 1). The baseline visit is comprised of:A clinical visit with a hepatologist or hepatology nurse wherein a detailed review of a subject’s medical history, a special assessment of cirrhosis severity and cirrhosis related events or symptoms (including animal naming test [ANT] [23]) as well as previous and current pharmacological treatments is performed. Information on demographics and medical history is collected from the patient and from medical records.A detailed clinical examination including blood pressure, weight, height, waist and hip circumference, and assessment of relevant lifestyle factors.Questionnaires to assess disease burden and health-related quality of life (HRQoL).Comprehensive blood panels including markers for blood, electrolyte, liver, and lipid status as well as blood samples for biobanking.Vibration-controlled transient elastography (VCTE) and controlled attenuation parameter (CAP) with Fibroscan™.Tests of muscle strength and physical performance, including the Short Physical Performance Battery (SPPB), hand-grip strength (HGS), and Liver Frailty Index (LFI).Estimated body composition measured by bioelectrical impedance measurement according to clinical routine (only at University Hospital in Linköping).20 min MR examination including BCP with MAsS, portal flow, MRE, and HCC-screening.

**Fig. 1 Fig1:**
[figure not shown]
Study flow chart outlining patient recruitment, inclusion, data collection and follow-up. Created with BioRender.com

### Follow-up

After inclusion and collection of baseline data, follow-up visits are performed after 6, 12, 18 and 24 months (Table 3). The study includes 5 visits (4 MR-examinations and a final follow-up visit) with 6 months interval if no liver lesions are found on MR-examination. If a nodule is defined as LI-RADS > 3, the patient has reached a significant endpoint and no further study visits will be performed (follow-up data will be collected through chart review). If a LI-RADS-3 is found on MR-examination, the time interval between subsequent MR-examinations is shortened from every 6 months to every 4 months during a 12-month period. This adds an extra MR-examination for patients with LI-RADS-3 (cumulative total of 5 MR-examinations instead of 4 during the study period) and therefore the cumulative number of visits is also increased from 5 to 6 visits (Fig. 1).

**Table 3 Tab3:** Flow chart of inclusion and follow-up visits

Procedure/data collection	Baseline (visit 1)	Follow-up (visit 2–4)	End of study (visit 5)
**Evaluation incl/excl criteria**	X		
**Informed consent**	X		
**Demography**	X		
**Medical history**	X		
**Family history**	X		
**New diagnoses**		X	X
**Health changes**		X	X
**Life-style factors**	X	X	x
**Concomitant medications**	X	X	X
**Clinical work-up**	X	X	X
**HE-assessment (ANT)**	X	X	X
**QoL questionnaires**	X	X	X
**Muscle function test**	X	X	X
**FibroScan**	X	X	X
**Blood panels**	X	X	
**Blood samples for research**	X	X	
**MR-examination**	X	X	

After end of the study period, all participants are included in regular follow-ups and HCC-screening according to clinical praxis (i.e.*,* ultrasonography every 6 months).

### Questionnaires

Patients will undergo validated questionnaires to assess quality of life and validated physical functional tests relevant to cirrhosis:I.Patient reported quality of lifeEQ-5D-5L: This questionnaire was developed by the EuroQol Group in 2009 as a measure of health-related quality of life. The descriptive system comprises five dimensions: mobility, self-care, usual activities, pain/discomfort, and anxiety/depression [24].CLDQ: The chronic liver disease questionnaire (CLDQ) is a self-reported questionnaire which has undergone repeated validation [25, 26].SHS: The short health scale is a validated self-administered visual analog scale questionnaire studied in both inflammatory bowel disease and irritable bowel syndrome [27–29].II.Muscle function and physical frailty testsSPPB and hand grip strength: Short Physical Performance Battery (SPPB) [30] and hand grip strength [31, 32] were originally developed and validated in elderly populations. However, they have shown to predict mortality in both elder and younger patients with severe liver disease [33].Hand-grip strengthLiver frailty index has been developed as an instrument to screen for frailty in patients with cirrhosis.

### Blood panels

Fasting blood samples will be collected from participants after an overnight fast. Samples will be stored at the Linköping Biobank Facility. The biobank facility is a state-of-the-art facility for quality-controlled storage in secure freezers. Collected samples are outlined in Fig. 2, from all participants blood, serum and plasma will be collected.

**Fig. 2 Fig2:**
[figure not shown]
Overview of blood sample acquisition and biorepository. Created with BioRender.com

All subjects consent so that samples can be transferred within and outside the EU/EEA and that samples can be sent for analyses to private companies in the biotechnology and/or pharmaceutical industry.

### Clinical hematology/biochemistry/immunology/virology

Several blood, serum and plasma markers will be analyzed (Table 4) to obtain a biochemical profile and to calculate previously identified biomarker algorithms associated with prognosis in cirrhosis (i.e.*,* MELD, CPT).

**Table 4 Tab4:** Detailed blood/serum/plasma work-up

Blood/Serum/Plasma markers	
**Complete blood count**	
• Hemoglobin, hematocrit, mean corpuscular value, mean corpuscular hemoglobin, mean corpuscular hemoglobin concentration, platelets, white blood cells.	
**Liver tests**	
• Albumin, bilirubin, ALT, AST, ALP, γGT, PT (INR), ammonia, high sensitive C-reactive protein	
**Iron studies**	
• Iron, transferrin saturation, total iron binding capacity, ferritin	
**Minor kidney function panel**	
• Sodium (Na), potassium (K), creatinine	
**Metabolic tests**	
• Cholesterol, triglycerides, LDL, HDL. fasting glucose, insulin, apolipoprotein AI and B	
**Direct alcohol marker**	
• Phosphatidylethanol	

*Abbreviations:*
*ALP* alkaline phosphatase, *ALT* alanine aminotransferase, *ANA* antinuclear antibody, *AST* aspartate aminotransferase, *γGT* gamma-glutamyl transferase, *INR* international normalized ratio, *PT* prothrombin time

### Vibration-controlled transient elastography

Transient elastography (TE) relies on a transient mechanical vibration used to induce a shear wave in a tissue. The propagation of the shear wave is then tracked using ultrasound to assess the shear wave speed. A specific implementation of 1D-TE, vibration-controlled TE (VCTE), has been developed to assess the average liver stiffness that correlates with liver fibrosis assessed by liver biopsy [33]. However, several studies have shown liver elasticity to also correlate with the risk of liver-related morbidity and mortality in patients with, and without, liver cirrhosis. In this study, it will be implemented using FibroScan®, including M- and XL-probe as well as Controlled attenuation parameter (CAP). CAP measures liver ultrasonic attenuation on the signals acquired by the FibroScan®. Principles of CAP measurements has been described elsewhere [34].

### Magnetic resonance imaging

MRI data acquisition is performed using a 3 T MRI scanners, Philips Ingenia (Philips Healthcare, Best, The Netherlands) at the Center for Medical Imaging and Visualization (CMIV), Linköping University Hospital and 3 T MR-scanners, Siemens Vida (Siemens, Erlangen, Germany) at the County Hospital in Jönköping and the District Hospital in Eksjö. We have devised a multimodal MR-protocol for this project that includes a range of specific MR-techniques (Table 5). In short, the protocol includes determination BCP with MAsS, MRE, and HCC screening.

**Table 5 Tab5:** Overview of the 20-min MRI examination. The sequences are listed in the scan order and highlighted in bold text. The imaging markers stemming from the individual sequences are listed in the last row. The body-composition profiling sequences (BCP) differ depending on abdominal or thigh coverage; in the abdominal sequences visceral adipose tissue (VAT) and abdominal subcutaneous adipose tissue (BCP) volumes as well as spinal erectors fa-free muscle volume (FFMV) and muscle fat infiltration (MFI) are measured. In the thigh sequences thigh FFMV and MFI are measured. The liver proton density fat fraction (PDFF) is measured using the mDixon quant sequence. The T2* liver sequence can be used to measure liver iron content (LIC). The dynamic Dixon sequences taken at 0,45,70,180 after bolus injection of gadoterate meglumine (Dotarem®) can measure signal intensity (SI) contrast based hepatobiliary markers. Lastly the two MRE sequences can measure the liver stiffness (|G***|**)

Sequence Name	BCP-Abdomen	BCP-Thigh	mDixon Quant	T2* Liver	mDixon Dynamic	MRESE	MREGRE
Mode	T1-weighted	T1-weighted	Quantitative Imaging	T2-weighted	Dynamic Imaging (0/45/70/180 s)	MR Elastography	MR Elastography
TR/TE (ms)	“shortest”/1 (3.4/0.98)	“shortest”/"shortest” (3.5/1.13)	“shortest”/"shortest” (6.9/0.96)	“shortest”/2.30 (8.2/2.3)	“shortest”/"shortest” (3.2/1.14)	1000/53.84	50/"shortest” (50/20)
Echo-train length	2	2	6	N/A	2	1	1
Flip angle (°)	10	10	3	10	10	90	30
no. slices	37	71	77	37	131	4	4
FOV RL/AP/FH (mm)	530/371/222	540/368/284	400/350/231	530/371/222	380/312.14/229.25	370/314.5/43	450/403.1/43
ACQ voxel size RL/AP/FH (mm)	3.3 × 3.6 × 6	2 × 2.2 × 4	3 × 2.99 × 3	2.20 × 3.59 × 6	1.75 × 1.75 × 3.5	4.67 × 4.67	1.5 × 4.67
ACQ matrix size	160 × 104	264 × 167	132 × 118	240 × 102	216 × 178	80 × 66	300 × 86
Reconstruction matrix	160	288	192	240	448	320	384
NSA		1	1	1	1	1	1
Breath hold	“yes”	“no”	“yes”	“yes”	“yes”	“yes”	“yes”
Compressed SENSE	“no”	“no”	“no”	“no”	“yes” (4)	“no”	“no”
Imaging marker(s)	VAT, ASAT, liver volume, spleen volume, spinal erectors, FFMV and MFI	Thigh FFMV and MFI	PDFF	LIC	SI	(|G*|)	(|G*|)

The body composition includes thigh fat-free muscle volume (FFMV) and muscle volume z-sore (FFMVz), thigh muscle fat infiltration (MFI) and sex-adjusted MFI, liver fat content (PDFF), visceral adipose tissue volume (VAT), abdominal subcutaneous adipose tissue volume (ASAT), spleen volume, spinal erector FFMV and MFI as well a skeletal muscle index at the 3rd lumbar vertebrae (L3-SMI; Fig. 3) measured by AMRA Medical AB (Linköping, Sweden) [21, 35–38]. 2D MRE (Resoundant, USA) is acquired as shown in Table 5 and processed as per the QIBA guideline [39]. HCC screening by aMRI will be conducted using standard gadolinium contrast agent (Dotarem®) and radiological reading.

